### Assessments

The data collection methods were developed and refined for acceptability from a previous pilot [21]. All participants will complete measures before randomization and at equivalent time frames post intervention and follow-up. Posttest completion will be immediately after the 6-week intervention (approximately 6-8 weeks after the completion of the prequestionnaire), and the follow-up questionnaire will be completed 6 weeks after the posttest. Participants will be sent online survey links and reminders using the REDCap database.

### Primary Outcome Measures

The primary outcome measures used in this study are as follows:

The Mental Health Continuum short form is an internationally applied and thoroughly validated self-administered rating scale that contains items that measure 3 aspects of well-being: emotional, social, and psychological. Participants are asked the degree to which they have experienced emotional, social, and psychological well-being over the past month. The form includes a 6-point Likert scale from 0=never to 5 every day. Scores on this scale can range from 0 to 70, and higher scores indicate higher levels of well-being [23].The *Depression, Anxiety, and Stress Scale* is an internationally applied and thoroughly validated self-administered rating scale that measures levels of depression, anxiety, and stress. Participants are asked the degree to which they have experienced depression, anxiety, and stress over the past month. A 4-point Likert scale is used from 0 (did not apply to me at all) to 3 (applied to me very much or most of the time) within each of the 3 domains. Normal scores for depression, anxiety, and stress ranged from 0 to 4, 0 to 3, and 0 to 7, respectively, and scores above these ranges indicate mild to extremely severe levels in each domain [24,25].

### Secondary Outcome Measures

The secondary outcomes measures used in this study are as follows:

The *Coping Orientation to Problems Experienced* inventory is an internationally applied measure that evaluates an individual’s levels of coping [26].The *General Help Seeking Questionnaire* is a measure that will be used to measure help-seeking behaviors [27].The *Social Connectedness Scale* will be used to measure an individual’s perceptions of social connectedness [28].The *Mental Health Literacy Scale* will be utilized to measure an individual’s level of psychoeducation [29].The *General Self-Efficacy Scale* will be employed to measure self-efficacy [30].The *Attribution of Responsibility for Parental Mental Illness Measure* was designed for the project to measure how responsible participants felt for their parents’ issue. The measure builds on attributional theory [31] and other research that has found that young people often blame themselves for their parent’s issue and consequently feel responsible for *fixing* it [32]. Examples of items were “I sometimes think my parent's illness is my fault.” Items are scored on a 7-point Likert scale ranging from 1 (strongly disagree) to 7 (strongly agree).

### Interviews: Determining Feasibility, Acceptability, and Safety

Individual interviews will be conducted with available (n=8) facilitators 1 to 2 weeks post the intervention to obtain their feedback on the training and the intervention in terms of feasibility, ease of use, practicality, and responsiveness. Individual interviews will also be conducted with 8 to 10 consenting mi.spot participants. Interview schedules for participants will be organized around safety as well as intervention acceptability, defined by the perceived benefit of the intervention and participants’ self-reported confidence in change [33]. If applicable, participants will be asked for their reasons for poor engagement or dropout.

### Usage

The total number and average length of log-ins will be recorded over 6 weeks. The number of attendees at each of the 6 weekly sessions, the number of participants who used the mi.thoughts.spot, and the number of participants who posted messages on the threads (including keeping track of repeat users) will be recorded. The number of facilitator-initiated and participant-initiated one-to-one sessions will also be recorded.

### Reimbursement

At the end of the 3 assessment periods, participants who complete all questionnaires will receive a AUD $50 (US $32) electronic gift voucher to use in selected stores (not for alcohol or tobacco). Intervention participants who engage in an interview will be paid with AUD $20 (US $12.85) voucher. Payment is provided in recognition of their time and to encourage completion/engagement.

### Participant Numbers

A total of 70 18- to 25-year-olds will be recruited. Participant numbers were initially determined by a power calculation indicating that a minimum of 44 participants, with Crit F=3.10 (using GPOWER 3.1, assuming 2 groups and 3 repetitions, a small effect size, an alpha of 5%, and power of 95%), will be required. However, based on previous dropout rates (the pilot study), it was considered that over the time frame of data collection (including the longer frame of the wait-list controls), there may be a dropout rate of up to 40%. As a consequence, recruitment numbers were increased to 70.

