**Conclusions:**

Study results will provide reliable evidence on a web-based intervention that has the potential to make a difference to the lives of many vulnerable young adults. Implementation guidelines are needed to embed the intervention in different service sectors.

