## Results

### Data Analysis

The impact of mi.spot on participants will be examined at pre, post, and follow-up time periods using analyses of variance on each of the measures outlined above. There will be a within-subjects factor (time) and a between-subjects factor (intervention/control). Data analysis will employ the intention-to-treat principle by including all participants in the analyses.

Interview data will be analyzed within a qualitative framework using interpretative phenomenological analysis (IPA). IPA is an approach that examines participants’ experiences and meanings of a phenomenon [34], and in this case, the facilitator’s and participants’ experiences of mi.spot. IPA also provides a structure for coding and categorization of data [34] and will be used to develop responses to questions regarding feasibility and acceptability. Before analysis, respondent validation will occur, a process that entails providing participants with a copy of their transcript and an invitation to delete any information they believe may be identifiable and/or modify existing or add any information. A second researcher will independently analyze one third of all transcripts. Rather than a numerical index of agreement, consensus will be reached by discussion and referring back to participants’ transcripts.

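### The stated 95% power for a small effect with 44 participants does not hold: at the program's default settings, 44 is the answer for a medium effect (f = 0.25)

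*Protocol article*

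**What the plan says.** Participant Numbers in the protocol article reports a "minimum of 44 participants, with Crit F=3.10 (using GPOWER 3.1, assuming 2 groups and 3 repetitions, a small effect size", at alpha 5% and power 95%. To allow for dropout of up to 40%, "recruitment numbers were increased to 70". The effect size is given only as a word. The correlation between repeated measures and the sphericity correction, both of which the program requires, are not reported.

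The Data Analysis section describes the matching model: an analysis of variance on each measure, with time (three assessments) within subjects and arm (two groups) between subjects.

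**The concern.** The parts of the sentence do not fit together. By the usual convention for Cohen's f, small is 0.10 and medium is 0.25. A two-arm, three-visit design with 44 people would not normally have 95% power for f = 0.10, and 44 is the figure that the program's defaults return for f = 0.25.

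What is at stake is how the primary outcomes are read. If the record says 95% power for a small effect, a reader may take a non-significant result on well-being or on depression, anxiety and stress as good evidence that not even a small benefit exists. Under most correlations the design does not support that inference.

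**Working it through.** **Inputs from the article (Participant Numbers):** total N = 44, critical F = 3.10, k = 2 groups, m = 3 repetitions, alpha = 0.05, power = 0.95, effect "a small effect size", recruitment target 70.

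**Assumed, because not stated:** correlation ρ = 0.5 and sphericity ε = 1 (the program defaults), with ρ then varied.

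**1. Which test was used.** For the within-subject or interaction test, df1 = (k − 1)(m − 1) = 2 and df2 = (N − k)(m − 1) = 42 × 2 = 84. F(0.95; 2, 84) = 3.105, which agrees with the printed 3.10 if truncated. The between-groups test has 1 and 42 df and a critical value of 4.07. The printed value therefore belongs to the within or interaction test. It does not identify f, because it depends only on N, k, m and ε.

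**2. Reproducing 44.** Power comes from the noncentral F distribution with λ = N·m·f²/(1 − ρ).
- f = 0.25, N = 44: λ = 44 × 3 × 0.0625/0.5 = 16.5, power 95.6%.
- f = 0.25, N = 42: λ = 15.75, power 94.6%.

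So at the defaults 44 is the smallest equal-group total reaching 95%, and it is reached at f = 0.25.

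**3. The same design at f = 0.10, ρ = 0.5.**
- N = 44: λ = 44 × 3 × 0.01/0.5 = 2.64, power 27.8%.
- N = 70 (everyone analysed): λ = 4.2, power 42.5%.
- 95% power requires N = 260.

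**4. Dependence on the unstated correlation (f = 0.10, ε = 1).** The N = 70 column uses the same formula with 2 and 136 df.

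| ρ | λ at 44 | Power, N = 44 | λ at 70 | Power, N = 70 | N for 95% |
|---|---|---|---|---|---|
| 0 | 1.32 | 16% | 2.10 | 23% | 518 |
| 0.3 | 1.89 | 21% | 3.00 | 32% | 362 |
| 0.5 | 2.64 | 28% | 4.20 | 43% | 260 |
| 0.7 | 4.40 | 44% | 7.00 | 65% | 156 |
| 0.8 | 6.60 | 61% | 10.50 | 83% | 106 |
| 0.9 | 13.20 | 90% | 21.00 | 99% | 54 |

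To reach the λ of 16.5 that N = 44 has at f = 0.25, f = 0.10 needs 1 − ρ = 44 × 3 × 0.01/16.5 = 0.08, that is, ρ = 0.92.

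**5. What f = 0.25 means between arms.** Take arm differences of 0, d, d (in SD units) at the three visits. Their mean is 2d/3. Halving the deviations from it gives interaction effects of size d/3, d/6 and d/6. The mean square is (d²/9 + d²/36 + d²/36)/3 = d²/18, so f = d/√18. The pattern 0, d, 0 gives the same. Hence f = 0.25 is d = 0.25 × 4.243 = 1.06, and f = 0.10 is d = 0.42.

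**The case against.** The strongest reply is that the default settings are inferred, not documented. Other pairs give the same λ at N = 44: f = 0.20 with ρ = 0.68 (132 × 0.04/0.32 = 16.5) and f = 0.15 with ρ = 0.82 (132 × 0.0225/0.18 = 16.5). This stands. The document does not establish that f = 0.25 was entered; that is only the most natural reading. But neither 0.20 nor 0.15 is the conventional small value, and at f = 0.10 the required correlation of about 0.92 would be very high for self-report scales completed roughly six weeks or more apart. Either the label is wrong or an unusual setting has gone unreported.

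It also stands that 28% is not a fixed property of the design. It moves from 16% to 61% over correlations of 0 to 0.8, and power is higher again if all 70 contribute data.

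Two stronger readings are tempting, and the document supports neither.
- A reader might infer that the trial can detect only very large effects. The 1.06 SD figure belongs to 95% power, N = 44 and ρ = 0.5. At the same correlation, 80% power is reached at about d = 0.65 with 70 analysed and about d = 0.83 with 44.
- A reader might see the abstract's conclusion, "Study results will provide reliable evidence on a web-based intervention", as a repeat of the error. It is general wording in a study that also covers usage, safety, acceptability and feasibility, none of which rests on this calculation.

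Nor does the article say that a null result will be taken as evidence of no small benefit. The risk lies in what a reader would draw from the printed power.

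**Conclusion.** As printed, the power statement is wrong or missing the one setting that could make it true. With correlation 0.5 and sphericity 1, 44 participants give 95.6% power at f = 0.25 and 27.8% at f = 0.10. Between correlations of 0 and 0.8, power for f = 0.10 at 44 never exceeds about 61%. The conclusion rests on the conventional f values for small and medium and on the interaction test that the critical F points to. The individual percentages also rest on the assumed correlation and on sphericity of 1.

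The error matters because this sentence is the article's only justification of sample size. It does not invalidate the design.

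**What to change.** In Participant Numbers, state the numerical f, the correlation and the sphericity value that were entered. If the defaults were used, describe the effect as medium: f = 0.25, equivalent to about 1.06 SD between arms at one or both post-baseline visits. Then give the power for f = 0.10 at 44 and at 70 as conditional on the correlation (28% and 43% at 0.5, with the range from the table), so that a non-significant result is not read as excluding a small benefit.

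The cost is a few sentences and a less favourable stated power. Enrolment, allocation, outcomes and tests are unchanged, and the abstract's conclusion needs no edit on this account.

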**Methods:**

Participants will be recruited through social media and clinician referral. A total of 70 Australians, aged 18 to 25 years, who grew up with parents with a mental illness or substance use concern will participate in a 2-arm parallel randomized controlled trial. The assessment will consist of a baseline measurement and 2 follow-up periods, posttest and 6-week follow-up, using the Mental Health Continuum short form; the Depression, Anxiety, and Stress Scale; the Coping Orientation to Problems Experienced inventory; the General Help Seeking Questionnaire; the Social Connectedness Scale; the Mental Health Literacy Scale; the General Self-Efficacy Scale; and the Attribution of Responsibility for Parental Mental Illness Measure. Impact will be examined at pre, post, and follow-up time periods using analyses of variance that will include a within-subjects factor (time) and a between-subjects factor (intervention/control). Facilitator interviews will ascertain intervention feasibility. Participant interviews will ascertain intervention acceptability. Interview data will be analyzed within a qualitative framework. Usage (data analytics) across site features and several indicators of clinical safety will also be reported.

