### Allocation/Randomization

After completing baseline data collection, participants will be randomly allocated to 1 of the 2 study groups. Randomization will occur via a random number generator (using Statistical Package for Social Sciences), and participants will be allocated according to the timing (ie, order) of signing up for the study to intervention and control conditions. A permutation block of 70 will be used to ensure equivalence of intervention and control group allocations. The project manager will be responsible for the randomization, and the researchers will be blinded to the allocation of participants to the intervention and control conditions. The random number allocation procedure will occur before the commencement of the study. Participants will be informed about their allocation in the initial telephone call and follow-up email.

Those allocated to the intervention group will be provided with a link to the password-protected intervention. Participants in the control group will be given information about other local and national services they can access, including online and face-to-face services. They will be offered the intervention after those in the intervention group complete the postintervention questionnaires (approximately 12 weeks after randomization).

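### At the plan's own 40% dropout ceiling, recruiting 70 leaves 42 completers rather than the stated minimum of 44; 70 covers dropout only up to about 37%

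*Protocol article*

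**What the plan says.** All the figures stand in one paragraph, Participant Numbers, of the protocol article. The target is "A total of 70 18- to 25-year-olds will be recruited". The power calculation gave "a minimum of 44 participants, with Crit F=3.10", from G*Power, "assuming 2 groups and 3 repetitions, a small effect size, an alpha of 5%, and power of 95" per cent. Citing dropout in the pilot and the longer time frame for wait-list controls, the article then states that "there may be a dropout rate of up to 40%. As a consequence, recruitment numbers were increased to 70".

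The total of 70 recurs in the Abstract ("A total of 70 Australians, aged 18 to 25 years") and sets the randomization block in Allocation/Randomization ("A permutation block of 70 will be used to ensure equivalence of intervention and control group allocations"). Those places repeat the number and contain no separate error. The Data Analysis section describes a time-by-group analysis of variance and says that all participants are included, on the intention-to-treat principle.

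**The concern.** The wording presents 70 as the result of allowing for up to 40% loss from a required 44. An allowance sized for a ceiling should still deliver the minimum when that ceiling is reached, and this one does not. Minimum, dropout allowance and recruitment target are printed together, and any two of them contradict the third.

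What is at stake is modest. Readers will judge attrition against the published allowance. If dropout fell between 37.1% and 40%, the trial would be inside its declared tolerance and yet below its declared minimum.

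**Working it through.** **Inputs from Participant Numbers:** minimum 44; dropout up to 40%; recruitment 70; 2 groups; 3 repetitions; alpha 5%; power 95%; critical F 3.10. Equal arms are taken from Allocation/Randomization.

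**Step 1: can 70 be reproduced from 44 and 40%?**
- Dividing by the retained fraction: 44/(1 − 0.40) = 73.3, so 74 (37 per arm). Check: 74 × 0.60 = 44.4, while 73 × 0.60 = 43.8 falls short.
- The common but incorrect method of adding 40%: 44 × 1.40 = 61.6, so 62.
- Neither gives 70, and no other section derives it.

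**Step 2: what does 70 leave?**
- At 40% dropout: 70 × 0.60 = 42, two below 44 (21 per arm rather than 22, if losses are even).
- Largest dropout that keeps 44: 1 − 44/70 = 26/70 = 37.1%.
- In whole people, 26 losses leave 44, 27 losses (38.6%) leave 43, and 28 losses (40%) leave 42.

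Steps 1 and 2 need no assumption beyond the printed figures.

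**Step 3: what does the shortfall cost in power?** The article gives no numeric effect size f, no correlation rho between repeated measures and no sphericity factor epsilon, so these are assumptions. For the time-by-group interaction with k groups and m repetitions, in the usual G*Power form:
- noncentrality λ = f² × N × m × epsilon/(1 − rho)
- degrees of freedom (m − 1)(k − 1) × epsilon and (N − k)(m − 1) × epsilon

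The plan's own 44 comes first. With f = 0.25, rho = 0.5 and epsilon = 1:

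| N | λ | df | Critical F | Power |
|---|---|---|---|---|
| 44 | 0.0625 × 44 × 3/0.5 = 16.5 | 2, 84 | 3.105 | 95.6% |
| 43 | 16.125 | 2, 82 | 3.108 | 95.1% |
| 42 | 15.75 | 2, 80 | 3.111 | 94.6% |

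Searching over even totals (equal arms), 44 is the smallest that reaches 95%. Its critical value of 3.105 agrees with the printed 3.10 if the last digit was cut rather than rounded. These inputs therefore reproduce the plan's figure. At 42, power is about 0.4 points under 95% and about 0.9 points under its value at 44.

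**Range over the unstated inputs.** With epsilon = 1, power depends on f and rho only through f²/(1 − rho), which is 0.0625/0.5 = 0.125 above. A pair such as f = 0.10 with rho = 0.92 has the same ratio (0.01/0.08 = 0.125) and gives the same 94.6% and 95.6%. Other pairs that do not reproduce 44 change the level of power much more than the gap:

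| f | rho | Power at 42 | at 44 | at 70 | at 74 |
|---|---|---|---|---|---|
| 0.25 | 0.5 | 94.6% | 95.6% | 99.7% | 99.8% |
| 0.10 | 0.9 | 88.7% | 90.2% | 98.7% | 99.1% |
| 0.10 | 0.5 | 26.7% | 27.8% | 42.5% | 44.7% |

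In every row the two completers between 42 and 44 are worth roughly 1 to 1.5 points.

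**The case against.** The strongest reply has three parts.

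- **The 40% is a ceiling.** The article says dropout may reach that level, not that it will. For any loss up to 37.1%, 70 does keep 44. This stands, and it confines the point to a narrow band and at most two people. It does not make the sentence right, because the ceiling is the condition the target was raised to meet.
- **Everyone is analysed.** Data Analysis includes all participants, so 42 completers need not be the number that carries the information. This partly stands: 94.6% is a complete-case figure, and how far participants with partial data would contribute cannot be judged from the article. It does not remove the inconsistency, because Participant Numbers itself treats dropout as the reason to go from 44 to 70.
- **The effect-size label matters more.** The inputs that reproduce 44 most readily use f = 0.25, usually called medium, whereas the article calls its effect small. That is a separate question with far larger consequences for power, and it neither causes nor excuses the dropout slip.

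A reader might infer that the plan forfeits its 95% power, or that the trial is underpowered because of this slip. The documents do not support that. The loss is about 0.4 points below 95%, arises only at the ceiling, and is computed from values the article never states.

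**Conclusion.** The allowance is wrong as written, and the point is minor. From printed figures alone, 70 at 40% dropout leaves 42 rather than 44, it covers 44 only up to 37.1% dropout, and 74 would match the stated inputs.

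The power consequence is conditional on f²/(1 − rho) = 0.125 (for example f = 0.25 with rho = 0.5), epsilon = 1 and complete cases: about 94.6% against 95.6%. That is too small to say that the slip materially underpowers the trial.

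Nor should the matching figure of 74 be read as a way to secure power for a small effect. If f were 0.10 with rho 0.5 (both assumed), power would be 44.7% even with 74 analysed.

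**What to change.** Keep 70 and correct the sentence in Participant Numbers in one of two ways:

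- describe 70 as allowing for up to 37% dropout while retaining 44; or
- keep the 40% ceiling, say that it leaves 42 completers, and give the power for 42 together with the numeric effect size and correlation actually used in the calculation.

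The second is the better choice if the pilot really supports 40%, because it leaves that assumption intact and also puts the missing inputs on record.

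The cost is one sentence and a slightly less favourable figure. No change is needed to recruitment, to the randomization block of 70 or to the analysis. The Abstract already reports 30 + 34 = 64 participants enrolled by 2 October 2019, so restating the allowance is more proportionate than moving the target.

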## Results

### Data Analysis

The impact of mi.spot on participants will be examined at pre, post, and follow-up time periods using analyses of variance on each of the measures outlined above. There will be a within-subjects factor (time) and a between-subjects factor (intervention/control). Data analysis will employ the intention-to-treat principle by including all participants in the analyses.

Interview data will be analyzed within a qualitative framework using interpretative phenomenological analysis (IPA). IPA is an approach that examines participants’ experiences and meanings of a phenomenon [34], and in this case, the facilitator’s and participants’ experiences of mi.spot. IPA also provides a structure for coding and categorization of data [34] and will be used to develop responses to questions regarding feasibility and acceptability. Before analysis, respondent validation will occur, a process that entails providing participants with a copy of their transcript and an invitation to delete any information they believe may be identifiable and/or modify existing or add any information. A second researcher will independently analyze one third of all transcripts. Rather than a numerical index of agreement, consensus will be reached by discussion and referring back to participants’ transcripts.

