### Objectives

This paper describes the protocol for a randomized controlled trial for the mental illness; supportive, preventative, online, targeted (mi.spot) intervention. It is hypothesized that following the mi.spot intervention, young adults will report the following:

Significant improvements in mental health and well-being (primary outcomes)Significant improvements in coping, social connectedness, and attribution of responsibility for parental mental illness (secondary outcomes)Significant increases in help seeking and mental health literacy (secondary outcomes).

Furthermore, the study will determine what components of the site participants use and do not use, along with their views about intervention safety and acceptability. Facilitators’ views of the feasibility of the intervention will also be sought.

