## Methods

### Design

This 2-arm parallel randomized controlled trial will compare outcomes at posttest and 6-week follow-up for mi.spot and control participants. The protocol is in accordance with the Consolidated Standards of Reporting Trials of Electronic and Mobile HEalth Applications and onLine TeleHealth checklist. The study was undertaken in 2019. The protocol was registered by the Australian and New Zealand Clinical Trials Register on May 5, 2019. The registration number is ACTRN12619000335190.

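### The repeated-measures ANOVA treats baseline as an outcome level and names no deciding effect; a baseline-adjusted between-arm difference at posttest would settle what counts as benefit, usually with some gain in power

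*Protocol article*

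**What the plan says.** The Data Analysis section of the protocol article fixes the model: "The impact of mi.spot on participants will be examined at pre, post, and follow-up time periods using analyses of variance", applied to each measure. It adds: "There will be a within-subjects factor (time) and a between-subjects factor (intervention/control". The Abstract describes the same model. No interaction, contrast, baseline adjustment or primary time point is named.

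The Objectives introduce the hypotheses with "It is hypothesized that following the mi.spot intervention, young adults will report the following"; neither that sentence nor the list after it refers to the control group. The Design section does: the trial "will compare outcomes at posttest and 6-week follow-up for mi.spot and control participants".

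The Participant Numbers section gives "a minimum of 44 participants, with Crit F=3.10" (G*Power, "assuming 2 groups and 3 repetitions, a small effect size, an alpha of 5%, and power of 95" percent). It then says "there may be a dropout rate of up to 40" percent, and that "recruitment numbers were increased to 70".

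**The concern.** A two-factor ANOVA over three occasions returns three tests: time, arm, and time by arm. Only the tests that involve arm rest on randomization. As printed, the hypotheses could be met by a time effect, which pools both arms and would pick up any change they share. Such change is plausible. Participants are volunteers, controls are given information about other services, and the Limitations section concedes that controls may seek support elsewhere.

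The second issue is efficiency. With about 42 completers the trial has little power to spare. The 2-df interaction removes stable differences between people by comparing change within person, but for any one visit it uses baseline less efficiently than covariate adjustment does. A significant result also says only that the two profiles differ somewhere. It gives no direction, and no single effect with an interval.

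**Working it through.** **Inputs from the article.** Minimum N 44, critical F 3.10, 2 groups, 3 repetitions, alpha 0.05, power 0.95; recruitment 70; dropout up to 40%, so 70 × 0.6 = 42 completers. Arms are taken as equal.

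**Assumed, because the article gives no figure.** Correlation ρ between occasions (equal for all pairs, sphericity), effect size d in SD units, and the size of any shared trend. Ranges are shown.

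**1. The plan's own figure.** For time and for time by arm alike, λ = 3Nf²/(1−ρ) with 2 and 2(N−2) df. With N = 44, f = 0.25 and ρ = 0.5, λ = 3 × 44 × 0.0625/0.5 = 16.5. The critical F(2, 84) is 3.105 and power is 95.6%. The arm main effect has 1 and 42 df and critical F 4.07, so it is excluded. The time effect and the interaction give identical results, so the stated figures cannot show which was meant. (That f = 0.25 is needed to recover 44, against the conventional 0.10 for a small effect, is a separate matter.)

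**2. Shared improvement, no treatment effect.** Both arms move 0, 0.4, 0.4 SD. The sum of squares about the mean (0.267) is 0.1067. Then λ = N × 0.1067/(1−ρ) = 42 × 0.1067/0.5 = 8.96, and the critical F(2, 80) is 3.111. The time effect is significant in 75% of trials. Other values at N = 42:

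| Shared shift (SD) | ρ = 0.5 | ρ = 0.7 |
|---|---|---|
| 0.2 | 24% | 38% |
| 0.3 | 49% | 72% |
| 0.4 | 75% | 93% |
| 0.5 | 92% | 99% |

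The interaction stays at its nominal 5% throughout.

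**3. Use of baseline, like for like.** At a single visit, a change score has variance 2(1−ρ) and a baseline-adjusted score 1−ρ² (SD = 1). At ρ = 0.5 these are 1.00 and 0.75.

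**4. Power of the two tests, sustained d = 0.5, N = 42.**
- Interaction: λ = (N/4) × SS/(1−ρ), where SS for arm differences (0, 0.5, 0.5) is 0.1667; df 2 and 80. At ρ = 0.5, λ = 10.5 × 0.1667/0.5 = 3.50.
- Adjusted posttest contrast: λ = (N/4) × d²/(1−ρ²); df 1 and 39. At ρ = 0.5, λ = 10.5 × 0.25/0.75 = 3.50.

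The ratio of the two λ values is 1.5/(1+ρ). At ρ = 0.5 they are equal, and the gain comes from spending 1 df instead of 2.

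| ρ | Adjusted posttest | Interaction |
|---|---|---|
| 0.3 | 38% | 27%* |
| 0.5 | 45% | 36% |
| 0.7 | 60% | 55% |
| 0.8 | 75% | 74% |
| 0.9 | 95% | 97% |

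*26.5% before rounding.

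At the effect that reproduces N = 44 (f = 0.25 corresponds to d = 0.25 × √18 = 1.06), the comparison is 97.8% against 95.6%.

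**5. Effect that grows after posttest.** With d = 0.25 then 0.5, ρ = 0.5 and N = 42, SS = 0.125. The interaction has λ = 2.625 and power 28%. The adjusted posttest contrast has λ = 0.875 and power 15%.

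**6. Adjusted mean of both visits.** Variance is (1+ρ)/2 − ρ², which is 0.50 at ρ = 0.5. Power is 61% for the sustained effect (λ = 10.5 × 0.25/0.50 = 5.25) and 39% for the growing effect (mean d 0.375, λ = 2.95).

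**7. Timing of the visits.** The Allocation/Randomization section offers controls the intervention about 12 weeks after randomization. The Recruitment and Screening section has controls complete their last questionnaires at 13 to 14 weeks. The follow-up comparison may therefore include controls who already have access; the posttest comparison, at 7 to 8 weeks for controls, does not.

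**The case against.** The strongest reply is that the between-arm intent is already there. The Design section states it, the model contains the arm factor, and the hypotheses sit under a randomized-trial protocol. A time effect pooling wait-list controls would not be a clean test of improvement after mi.spot anyway. Naming the interaction alone would guard against a shared trend. A journal article may also leave the deciding contrast to a fuller analysis plan.

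Much of this stands. A reader might infer that the authors will claim benefit from a time effect; no section says so, and the Design section points the other way. A reader might also infer that the trial was sized on the interaction, or on the time effect; the critical F supports neither over the other. It would be wrong to say that the interaction ignores baseline, since it compares change within person. Protection against a shared trend is not peculiar to ANCOVA.

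What does not stand is that this is only omitted detail. The article commits to a specific model with baseline as an outcome level, and prints hypotheses without a comparator. Those statements need changing whatever a fuller plan adds. The choice of posttest is a judgement, because the article makes no time point primary, but the wait-list timing gives a reason for it.

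**Conclusion.** The point holds with conditions. The printed model, hypotheses and power statement do not fix which effect decides benefit, and one admissible reading is a comparison that randomization does not protect. Under that reading, a shared 0.4 SD improvement would be taken for impact in about 75% of trials (N = 42, ρ = 0.5; both the shift and ρ assumed).

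The gain in power from adjustment is usual, not guaranteed. It is about 9 points at d = 0.5 and ρ = 0.5, about 2 points at the effect that recovers N = 44, nil near ρ = 0.8 and slightly negative at 0.9. A reader might infer that the adjusted posttest contrast is always stronger; it has roughly half the interaction's power (15% against 28%) if the effect doubles between posttest and follow-up. Nor does the 61% apply to it: that figure belongs to the mean of both visits. The case for the change rests first on a single, directed, between-arm estimate, and only second on power. It should be made, but it does not invalidate the trial.

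**What to change.** In Data Analysis, state that the primary test for each primary scale is the between-arm difference at posttest, adjusted for that scale's baseline score (ANCOVA, or the same contrast from a baseline-adjusted mixed model), reported with a 95% CI. Give the same contrast at follow-up as secondary. State that time effects are descriptive. In the Objectives, word each hypothesis as improvement relative to control.

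The 12-week wait-list offer and the 13-to-14-week control follow-up must be reconciled in the text. If that shows follow-up to be free of wait-list treatment, the baseline-adjusted mean of both visits is an alternative primary contrast with more power in both scenarios above.

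The cost is wording only: baseline measures are already taken on everyone before randomization. The price is the loss of power at posttest if the effect emerges late.
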